### Overall study design

The LeSA Project uses an effectiveness/implementation Hybrid Type 1 Design [48] to simultaneously test the effectiveness of TBRI for preventing non-medical use of opioids among JJ-involved adolescents and gain insight into facility-level obstacles that must be overcome if the intervention is to be implemented and sustained as part of JJ re-entry protocols. The overall study design includes (a) a delayed-start at the site level and (b) a randomized controlled trial at the participant level.

To address the logistical burden of protocol implementation and to control for the influence of other exogenous factors [49], participating sites are assigned to one of three Study Waves and proceed through three sequential study stages accordingly. Wave membership is determined by stratifying by state (3 sites in one, 6 in the other) and ranking by the number of youth served in descending order. For the state with 3 sites, one is assigned to each wave, with the highest populated site starting in Wave 1. For the state with 6 sites, two are assigned to each wave, with the highest and fourth-highest populated sites starting in Wave 1. Stage 1 - SRP data collection launches as soon as sites are ready. Stage 2 study activities are delayed by 1 month.

### Hybrid design: effectiveness trial

The effectiveness trial includes a comparison of youth enrolled in SRP to youth enrolled in SRP plus TBRI, whereby each facility serves as its own control. Because caregivers may need support after their youths’ release, three versions of TBRI are compared, with youth in the SRP + TBRI cohort being randomly assigned to one of three support formats: (1) TBRI Training only (no in-home TBRI support), (2) TBRI Training + Structured Coaching (4 sessions), and (3) TBRI Training + Responsive Coaching (2+ sessions, triggered by youth need/risk).

The effectiveness trial proceeds in 3 stages: Standard Reentry Practice (SRP) only (baseline control), SRP + TBRI, and Facility Sustainment (see Fig. 2). **Stage 1 - SRP**: sites engage in standard practice; study activities include youth and caregiver assessments over 18 months. Each site serves as its own control. A total of 120 youth/adult dyads are recruited across the nine sites. The length of SRP varies between 8 months (Wave 1) and 12 months (Wave 3). **Stage 2 - SRP + TBRI Intervention:** sites continue to engage in standard practice; TBRI intervention is delivered to youth and caregivers enrolled in the study; youth and caregiver assessments are conducted over an 18-month period. A total of 240 youth/adult dyads are recruited across the nine sites. **Stage 3 - Facility Sustainment**: youth/caregiver recruitment, baseline assessment, and interventions cease; youth and caregiver follow-up interviews continue; responsibility for implementing primary and secondary TBRI intervention components is transferred to the JJ facility.

**Fig. 2 Fig2:**
[figure not shown]
Recruitment and data collection timeline

At the participant level (see Fig. 3), for both SRP and SRP + TBRI stages, youth and safe adults are recruited/consented 2–3 months prior to discharge, and individually complete baseline at recruitment and follow-up interviews at 3- (within 2 weeks of discharge), 6-, 12-, and 18-months post-baseline. For dyads recruited during the Stage 2 – SRP + TBRI Intervention period, the primary TBRI intervention sessions begin after baseline assessment while the youth are in the residential facility. At the point of discharge, dyads are randomly assigned to one of 3 TBRI in-home support conditions, with probabilities equal to 1:3 within each site. This overall design enables comparison of TBRI versus SRP plus a randomized control trial comparing TBRI support conditions.

**Fig. 3 Fig3:**
[figure not shown]
**Research design: Randomized control trial (*****N*** **= 360 dyads).**
*Note*. TBRI In-Home Training: either Structured Coaching or Responsive Coaching; Virtual or physical in-home visits by a TBRI Practitioner. Responsive Coaching “trigger” would be (**a**) substance use (SU), (**b**) parent suspects SU, (**c**) presence of risk factors for SU

#### Randomization

Dyads are randomly assigned to TBRI support condition by the research project director using urn randomization until the recruitment target is met (minimum of 80 per arm; an average of nine per arm, per site). Urn randomization is used to balance the characteristics of youth by group on sex (male vs. female), race (Caucasian vs. other race), and primary speaking language (English vs. Spanish).

### Hybrid design: implementation overlay

The implementation overlay includes three types of research activities occurring throughout all three project stages: (1) documenting facility use of trauma-informed strategies and contextual factors (see *Measurement and outcomes*) that facilitate or impede the use of these strategies, (2) supporting facility efforts to become more trauma-informed and in their use of TBRI practices during daily interactions with youth (see *Support for the organizational TBRI intervention*), and (3) building the necessary infrastructure to sustain the primary and secondary TBRI intervention components after the project ends (see *Sustaining the primary and secondary TBRI intervention*).

Prior to the launch of Stage 1 - SRP, the research team and facilities work together to explore each facility’s needs and desire to implement trauma-informed strategies such as TBRI. Contextual factors and use of trauma-informed strategies are documented through surveys of JJ facility staff at four time points throughout the study: the beginning of Stages 1, 2, and 3, and the end of Stage 3 (see Fig. 2). This information is used to customize support for facilities seeking to implement TBRI across their system and to understand how contextual factors—specifically how the use of trauma-informed care at a facility level—moderate the effectiveness of the primary and secondary TBRI intervention.

#### Support for the organizational TBRI intervention

While the project focuses on the delivery of the primary and secondary TBRI intervention with youth and caregivers, all facilities are invited but not required to participate in the organizational TBRI intervention. All facilities receive two 1-day TBRI trainings as part of the LeSA project at the beginning of Stages 2 and 3 (see Fig. 2). Training focuses on basic constructs underlying TBRI and an introduction to TBRI principles and strategies. For facilities that elect to implement TBRI across their residential program and/or across their juvenile systems, additional support is provided by the research team. An important step is to develop a change team within each facility, ideally with representation from every level, including JJ leadership (e.g., Deputy Director), behavioral health staff (e.g., clinicians), and other staff with youth interaction (e.g., direct care, supervising officers). This group is responsible for leading TBRI implementation efforts within their system.

Facilities can participate in two types of activities to cultivate TBRI expertise: (1) coaching and support for how to adapt TBRI principles and strategies within their system and (2) TBRI Practitioner training for 2–4 facility staff to further support and sustain the implementation of TBRI. Using a train-the-trainer approach, these TBRI Practitioners then extend TBRI principles and strategy use across departments and levels of the system, demonstrating strategies, training staff, and providing internal expertise on ways to modify existing practices. These opportunities are provided at any point during the project.

#### Sustaining the primary and secondary TBRI intervention

Stage 3 – Facility Sustainment, affords a naturalistic investigation of sustainment of the intervention within the facilities after responsibility for intervention delivery has been transferred from the research center to the JJ facilities. Prior to the end of Stage 2 – SRP + TBRI, sites are asked to indicate whether they would like to continue offering the primary and secondary TBRI intervention after the effectiveness trial ends. Sites that choose to do so collaborate with the research team to develop a customized plan for transitioning intervention delivery to facility staff, using information collected as part of the effectiveness trial. Facilities can choose how best to implement the curricula so that it fits within their existing policy, practice, staffing, and financial constraints. Research staff provide training in all aspects of curriculum delivery and support initial efforts as needed. Specific details regarding facility implementation plans and inner/outer contextual factors that impact decisions will be documented [50].

### Study samples and recruitment

A total of nine residential facilities designed to address the behavioral and emotional needs of justice-involved youth serve as research sites for this project. Three are located in a Midwestern state and 6 in a Southwestern state in the U.S.A. Three are operated by the state JJ system, 4 by local JJ departments, and 2 by an independent agency. All sites are secure residential programs with medium security protocols, all receive referrals from JJ departments across a wide geographic region, and all provide educational, medical, and behavioral health services. At project start, 3 sites had incorporated TBRI into their trauma-informed care approach for 1–3 years, 2 were familiar with TBRI but not using principles and strategies, and 4 were unfamiliar with TBRI.

The project involves two target samples drawn from the nine facilities at rates proportional to current census/staffing levels. The effectiveness trial sample includes a total of 360 youth/caregiver (e.g., parent/guardian, extended family member) dyads recruited from participating JJ facilities over a 3-year period (approximately 10–15 dyads/year per site). Inclusion criteria include youth ages 15–18 at study enrollment who (a) are disposed to community supervision (i.e., probation) and receiving care in a secure JJ facility, (b) have no indication of active suicide risk, and (c) have worked with JJ staff to identify one caregiver that is willing to participate in the study. The implementation overlay sample includes approximately 203 (out of 810 potential participants with a 25% completion rate) JJ staff (facility staff and probation officers; an average of 22–23 per site) who work directly with youth during residential and/or community re-entry. Out of this sample, approximately 90 JJ staff (an average of 10 per site) are recruited for focus groups.

Research sites facilitate the identification and recruitment of family participants (e.g., connecting RAs to families). Brochures, consent and assent forms, assessment battery, and curricula are available in English and Spanish. Bilingual English and Spanish-speaking RAs are available for Spanish-speaking families in all research activities. The research protocol is approved by the Texas Christian University (TCU) Institutional Review Board (IRB) and by site research review committees (if applicable), and the local juvenile board (if applicable). Assessment data are collected via Qualtrics. Protocols are delivered via secure virtual platforms (e.g., Zoom, Microsoft Teams) or in-person, depending on the activity. Caregiver consent, parental/guardian permission for youth participation, and youth assent are obtained in writing by RAs prior to all research activities; youth provide consent in writing if they turn 18 during the study. Youth and caregivers are compensated separately for their time spent in assessments in an amount of $15 e-cards per assessment.

Research staff work with JJ facility leadership to determine participant lists for staff surveys and focus groups. All individuals with direct youth contact (e.g., case managers, educators, direct care staff, probation officers) receive an individualized link to a confidential survey administered via Qualtrics. Recruitment of newly hired staff occurs prior to each assessment. JJ leadership are asked to identify up to 10 individuals representing leadership and line staff, including admin, clinical supervisors, justice probation officers, clinical staff, direct care staff, for in-person focus groups. To avoid potential coercion, introduction of risk to subordinates’ disclosures, and/or biased/invalid focus group data, leadership and line staff are invited for separate in-person focus groups at each site. Consent is obtained prior to the first assessment by an RA and prior to each focus group interview. Staff participants receive an honorarium (e.g., a cup, group meal) for participation.

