The *primary TBRI intervention* is delivered while youth are in secure residential settings, within 3 months prior to discharge. Principles and strategies are learned and practiced in separate caregiver and youth group sessions, then strengthened in joint youth-caregiver sessions. The focus of caregiver sessions is on identifying and meeting youth needs, supporting appropriate self-expression, improving self-regulation, and developing healthier relationships. Youth are also trained in complementary sessions to develop skills and a deeper understanding of felt safety and trust. Key constructs are taught through playful engagement and role play for youth and caregivers to actively connect with one another while developing new skills.

The *primary TBRI intervention* is an adapted version of the TBRI Caregiver Curriculum [33, 37] and includes several components (see Tables 2-3): (1) Youth Trainings: 9, 45-min youth-only modules; (2) Caregiver Trainings: a 1-h individual introductory module and 9, 90-min caregiver-only modules; and (3) Nurture Groups: Youth and caregivers participate together in 4, 1-h joint-roleplay sessions. Both Youth and Caregiver Trainings are designed to be delivered in a group setting with three to five in each group; however, missed sessions can be delivered as individual sessions. Additional monthly “booster” nurture group sessions are delivered in instances where the youth’s discharge is extended beyond the original expected date.

**Table 2 Tab2:** A Brief Overview of TBRI Curriculum (Caregiver Trainings, Youth Trainings, Nurture Groups)

Primary TBRI Intervention			
**Module**	**Youth and Young Adult Curriculum **	**Caregiver Curriculum**	**Nurture Group Activity (joint roleplay by youth/caregivers)**
0	• Introductions and Expectations • Familiarization with the Virtual Platform • Overview of the Tools for Learning and the Youth Workbook • Group rules: Designed for Felt Safety among all Participants	• Introductions and Expectations • Familiarization with the Virtual Platform •Overview of the Tools for Learning and the Caregiver workbook • Group rules: Designed for Felt Safety among all Participants	• N/A
*Session 1: TBRI: Introduction and Overview*			

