*Public health and safety outcomes* include opioid-related health, opioid use overdose, use of other illegal substances, recidivism, and SU or MH treatment records. *Opioid-related health* outcomes include SU treatment, hospital visits related to SU, diagnosis, overdose, and receipt of Narcan [65]. *Recidivism* information (re-arrest, re-adjudication), urinalysis results, and *treatment* records (type of referral, service receipt) come from JJ facility youth records [65]. For these data, sharing agreements between each state-level JJ facility and the research institute are established, specifying how de-identified records are shared, stored, and analyzed, following models from previous collaborations [66]. *Background information* on youth is extracted from existing JJ youth records (e.g., offense, disposition decision, supervision level, offense history including truancy, and prior SU or MH diagnosis).

Youth and caregivers provide different pieces of background information that serve as covariates or moderators, including demographics (e.g., age, sex, race/ethnicity, employment, education). Caregivers are also asked about their SU (TCU DS 5-OS) [52] and relationship with their own caregiver using the Experiences in Close Relationships-Relationship Structures (ECR-RS) [63]. Other potential covariates include number and type of ACEs [67], youth self-reported social exposure to substance use (e.g., “How often does the adult who is most important to you drink alcohol?”) [53], services youth and family received (adapted from the Child and Adolescent Services Assessment) [68], caregiver motivation in treatment participation (Parent Motivation Inventory; PMI) [69], parenting strain (Caregiver Strain Questionnaire-Revised Short Form; CGSQ-SF) [70], and parental resiliency (Resiliency of Self-Efficacy Scale; RS) [71]. Participants are also asked to respond to two open-ended questions regarding the impact of COVID-19 (e.g., “How is the COVID-19 crisis affecting you or has affected you?”). *Monthly phone check-ins* with youth assess 8 indicators of any opioid use; any alcohol, other drug use; truancy; trouble with the law, increases in depression, increases in anxiety, increases in the stress in relationship with the safe adult in the past month.

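### Caregiver willingness to take part means assessments only in Stage 1 but assessments plus about 17 to 18.5 hours of sessions in Stage 2, so the non-randomized H1 comparison is open to differential selection at consent, and the stated analysis does not adjust for it

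*Protocol article*

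**What the plan says.** Under Study samples and recruitment, one set of criteria covers the whole effectiveness sample. Criterion (c) is that youth "have worked with JJ staff to identify one caregiver that is willing to participate in the study".

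Hybrid design: effectiveness trial describes what taking part involves. In Stage 1, "sites engage in standard practice; study activities include youth and caregiver assessments over 18 months". In Stage 2 the assessments continue and "TBRI intervention is delivered to youth and caregivers enrolled in the study". For the caregiver, the section on the intervention lists "a 1-h individual introductory module and 9, 90-min caregiver-only modules", and it adds that "Youth and caregivers participate together in 4, 1-h joint-roleplay sessions". In-home coaching follows in two of the three support arms.

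In both stages, "youth and safe adults are recruited/consented 2–3 months prior to discharge", and written consent precedes any research activity. Randomization takes place later, at discharge, and only among the support formats within the TBRI cohort. The SRP-versus-TBRI contrast therefore compares successive cohorts at the same sites, with each facility acting as its own comparator.

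The Data analysis plan tests H1 with a log-rank comparison of survival curves (PROC PHREG and PROC GLIMMIX, Sidak adjustment) on an intention-to-treat basis. It names no covariate for that test. Caregiver motivation, measured with the PMI, appears in Measurement and outcomes as one of several potential covariates. Table 4 shows it collected from caregivers at baseline and Month 3.

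**The concern.** A criterion that depends on willingness selects according to what people are asked to do. A caregiver happy to be interviewed but unwilling to commit to a multi-week course can say yes in Stage 1 and may say no in Stage 2. The stage defines the exposure and is settled before the family decides, so any such difference is built into H1 before TBRI begins.

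The article itself gives reason to think this trait is prognostic. The Background treats close family ties as protective against substance use, and the conceptual model has TBRI act through the caregiver. A family characteristic that predicts agreeing to the course could therefore also predict opioid initiation without TBRI. Part of any H1 difference could then reflect who enrolled. The same would carry into the SRP-versus-TBRI part of H4, whose effectiveness measure is the difference in time to initiation.

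**Working it through.** **1. Commitment by stage.**
- Stage 1: assessments at Months 0, 3, 6, 12 and 18.
- Stage 2: the same assessments plus the primary intervention. Caregiver-only time is 1 + 9 × 1.5 = 14.5 h and joint sessions are 4 × 1 = 4 h, 18.5 h in total.
- Table 2 numbers its modules 0 to 8. If the introduction is one of those nine, caregiver-only time is 1 + 8 × 1.5 = 13 h and the total is 13 + 4 = 17 h.
- Coaching (four sessions, or two or more) comes on top in two of three arms.

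**2. Order of events.** The stage at the site is set, then the family is approached and consents, then baseline is taken. In Stage 2, TBRI sessions and randomization among support formats follow. Selection at consent thus precedes randomization. It can affect SRP versus TBRI, but not the comparison among the three support arms.

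**3. What the safeguards cover.** Within-facility comparison removes stable differences between sites, whereas this selection acts between stages within a site. Intention to treat keeps enrolled caregivers who do not attend, but it never sees those who declined. The log-rank test, as stated, compares the cohorts as they come.

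**4. How large could it be?** The plan gives no consent or refusal rates, so there is no figure to reproduce. The yardstick is the planned contrast in the Power section, 35% versus 25%, or 10 points. What follows is illustration, and *w* and *r* are assumptions, not document figures.

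Let the SRP rate be 35% and TBRI have no effect. A share *w* of SRP-type families would also accept the course, with risk *r* relative to the rest, and Stage 2 enrols only such families. The risk in the rest is p0 = 0.35 / (w·r + 1 − w), the TBRI cohort shows r·p0, and the spurious difference is 0.35 − r·p0.

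Example: w = 0.4, r = 0.6 gives p0 = 0.35/0.84 = 0.417, a TBRI rate of 0.250 and a difference of 10.0 points.

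| Spurious difference (points) | r = 0.5 | r = 0.6 | r = 0.7 | r = 0.8 | r = 1 | r = 1.25 |
|---|---|---|---|---|---|---|
| w = 0.4 | 13.1 | 10.0 | 7.2 | 4.6 | 0 | −4.8 |
| w = 0.6 | 10.0 | 7.4 | 5.1 | 3.2 | 0 | −3.0 |
| w = 0.8 | 5.8 | 4.1 | 2.8 | 1.7 | 0 | −1.5 |

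Positive values favour TBRI. The last column (r = 1/0.8) covers the case in which the offer attracts higher-risk families; for w = 0.4, p0 = 0.35/1.10 = 0.318, the TBRI rate is 0.398 and the difference is −4.8.

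For r = 0.5 to 0.8, a two-sided 5% comparison of proportions with 120 and 240 youth would favour an ineffective TBRI in about 5% to 75% of trials, where 2.5% is nominal. This approximates the log-rank test.

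**5. Partial selection.** Step 4 assumes complete selection. A milder version takes initiation as 25% with a motivated caregiver and 40% otherwise, with half of Stage 1 caregivers motivated. If 65%, 75% or 90% are motivated in Stage 2, the spurious difference is 0.15 × 0.15 = 2.25, 0.25 × 0.15 = 3.75 or 0.40 × 0.15 = 6.0 points. A shift of the same 15 points the other way gives −2.25.

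**The case against.** The strongest reply is that the article shows no actual difference between the cohorts. A reader might infer that criterion (c) excludes reluctant caregivers in Stage 2, so that H1 compares families known to differ in motivation, in TBRI's favour. The text does not support this. Attendance is not an eligibility condition, missed sessions can be made up individually, and intention to treat keeps those who attend little, so a lukewarm caregiver can still enrol in Stage 2. The article gives neither the consent wording nor refusal rates by stage. The direction is also open: Stage 2 offers families a service and may draw those in more difficulty, whose youth are at higher risk.

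Other features narrow the gap. Safe adults in both stages agree to support re-entry and to long follow-up, and caregiver sessions are virtual, so distance is no barrier. Motivation, strain and relationship quality are measured at baseline, and the final covariate set may be fixed in an analysis plan that is not shown.

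All of this limits the strength of the claim. What remains is that consent covers different commitments, the stage is fixed beforehand, the contrast is not randomized, and the H1 analysis that the article does state is an unadjusted log-rank test. Having the PMI on a list of potential covariates does not put it into that analysis.

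**Conclusion.** The point holds as a risk of bias in H1, and in the SRP-versus-TBRI part of H4. It is not a demonstrated bias. The difference in commitment, 17 to 18.5 hours of sessions against none, follows from the document. Selection towards more engaged caregivers, and hence in favour of TBRI, is plausible, but neither its direction nor its size can be established. The illustrative range of 1.7 to 13.1 points rests on assumed values and complete selection. It shows only that selection alone could be comparable with the planned 10-point effect; other assumptions give zero or a reversed sign. H2 and the between-arm part of H4 are not affected.

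**What to change.** Make the primary H1 analysis a Cox model, for which PROC PHREG is already named, stratified by or adjusted for site, with baseline PMI as a prespecified covariate. Optional additions, also chosen in advance, are caregiver strain (CGSQ-SF) and the relationship measures (FAD, ECR-RS), all collected at baseline. Use baseline values only, since the Month 3 PMI may already reflect TBRI. Tabulate these measures by stage. Report numbers approached, eligible and refused by stage and site where records exist. State remaining selection at consent as a limitation of H1.

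The cost is small. No new data are needed, and the planned rates imply about 0.35 × 120 + 0.25 × 240 = 42 + 60 = 102 events, enough for a few covariates. The hazard ratio becomes conditional on the covariates, and missing PMI values need the imputation already planned.

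Adjustment can remove the bias only in part: the PMI is completed after consent with the stage known, so answers may depend on the stage, and caregivers who declined are never measured.

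I would leave the eligibility criterion as it is. Asking SRP caregivers whether they would attend a course not on offer costs them nothing to affirm, so it may not equalize selection, and a change during the trial would put Stage 1 under two sets of criteria.
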